### Sample size calculation

An estimation of the expectable effect size was based on the results of the pre-post study testing the initial efficacy of the program [22]. This study revealed a decrease in the percentage of persons with at least one RSOD occasion in the last month from 76% at baseline assessment to 68% at follow-up assessment. It is assumed that the improvements in the content and tailoring of the intervention will also result in an improved efficacy. Based on these considerations, it is assumed that the percentage of persons with at least one RSOD occasion in the last month at follow-up will be 76% in the control group and 66% or lower in the intervention group. A sample size of n = 322 in each study group would be required to have 80% power for a χ^2^-test (α = 5%, 2-sided) in order to detect this difference based on a calculation using *G-Power*
[25]. As students are nested within school classes, a potential design effect needed to be considered. Based on [22] an average cluster size of 10 study participants per school class and an intra-cluster correlation coefficient of 0.05 could be expected. This would result in a design effect of 1.45. Multiplying this design effect by the required size for an unnested sample (n = 322) results in a required sample size of n = 467 per study group and a total of n = 934 study participants.

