**Methods/Design:**

A two-arm cluster-randomised controlled trial with one follow-up assessment after 6 months will be conducted to test the efficacy of the intervention in comparison to assessment only. The fully-automated intervention program will provide an online feedback based on the social norms approach as well as individually tailored mobile phone text messages to stimulate (1) positive outcome expectations to drink within low-risk limits, (2) self-efficacy to resist alcohol and (3) planning processes to translate intentions to resist alcohol into action. Program participants will receive up to two weekly text messages over a time period of 3 months. Study participants will be 934 students from approximately 93 upper secondary and vocational schools in Switzerland. Main outcome criterion will be risky single-occasion drinking in the past 30 days preceding the follow-up assessment.

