**Study design.**

### Participants, setting and procedure

The *MobileCoach Alcohol* will be tested in vocational and upper secondary school students due to (1) their heterogeneous educational level and (2) their age range, primarily between 16 and 20 years of age. In this age group, alcohol consumption increases considerably compared to younger age [9] and the use of Internet and mobile phone text messaging is widespread [17]. Vocational and upper secondary schools in the Swiss Cantons of Zurich and Berne will be invited by prevention specialist centres in Zurich and Berne to participate in the study.

The vocational and upper secondary school students will be invited for study participation during a regular school lesson reserved for health education. They will be invited by junior scientists to participate in a study testing innovative channels of information about alcohol consumption. To ensure sufficient participation and, thus, representativeness of the sample [23], a reward of 10 Swiss Francs for participation in the study at both baseline- and follow-up assessment will be announced. Each student will receive a tablet computer for conducting the screening, baseline assessment, and study registration. Inclusion criterion for study participation is possession of a mobile phone. After receiving informed consent, study participants will be invited to choose a username and to provide their mobile phone number. Participants of the intervention group will receive additional questions that are necessary for tailoring the intervention content. Subsequently, participants in the intervention group will receive an individualised feedback based on the social norms approach on their tablet computer. During the subsequent 3 months, participants of the intervention group will receive one or two individually tailored text messages per week to reduce problem drinking. Participants of the assessment-only group will receive no intervention. Computer-assisted follow-up assessments after 6 months will be conducted by a junior scientist, within the participating school classes, during regular school lessons and using tablet computers.

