### Data analyses

Generalized Estimation Equation analyses (GEE) [41] will be used to test the efficacy of the intervention on the different outcome measures. Based on the scale level of the measurement and its distribution, logistic GEE-models, linear GEE-models or GEE-models for count variables will be applied. Potential baseline differences will be considered by adding additional baseline variables as covariates to the GEE-models. Both (1) complete case analyses (CCA) considering all study participants with available follow-up data and (2) intention to treat (ITT) analyses will be conducted. For the ITT analyses, the multiple imputations procedure (MICE) of STATA will be applied. Given the clustered nature of the data, robust variance estimators for all GEE-models will be computed, using the cluster option of STATA.

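### The 934 students to be enrolled equal the number needed for analysis, so the stated 80% power holds only if nobody is lost by 6 months

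*Protocol article*

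**What the plan says.** The Sample size calculation section gives a full derivation. The outcome is the percentage with at least one risky single-occasion drinking episode in the last month, assumed "at follow-up will be 76% in the control group and 66% or lower in the intervention group". The test is a chi-square test ("α = 5%, 2-sided"). "A sample size of n = 322 in each study group" "would be required to have 80% power". With 10 participants per class and an intra-cluster correlation of 0.05, the design effect is 1.45. "Multiplying this design effect by the required size for an unnested sample" gives 467 per group and 934 in total. Nothing further is added.

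The Methods/Design part of the abstract uses the same figure for the study sample: "Study participants will be 934 students from approximately 93 upper secondary and vocational schools in Switzerland". (Whether 93 counts schools or classes is a separate matter and does not affect this point.)

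The only follow-up is at 6 months. The Participants, setting and procedure section says it takes place "within the participating school classes, during regular school lessons and using tablet computers". The Data analyses section provides for "complete case analyses (CCA) considering all study participants with available follow-up data", alongside an intention-to-treat analysis with multiple imputation.

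**The concern.** The analysis section expects some 6-month outcomes to be missing, while the sample size section assumes that none will be. The figure that gives 80% power is a number of students with an observed outcome, yet it also serves as the number to enrol. Follow-up is a single assessment in class, and the article describes no other route for students who are absent that day or have left the class.

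What is at stake is the power figure against which the result will be read. If some students are lost, the trial has less power for the stated difference than the protocol reports.

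This is not a detail that can be left to an analysis plan. The article carries the calculation through to a final number, and an allowance made elsewhere would change that number or the power attached to it.

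**Working it through.** **Inputs from the protocol article.** Control 76%, intervention 66%, two-sided alpha 5%, power 80%, class size m = 10, intra-cluster correlation 0.05, 467 per arm enrolled.

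**Input not in the documents.** The proportion lost by 6 months, f. It is varied from 5% to 30% as an assumption.

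**Step 1: reproduce the plan's figure.** Pooled two-proportion formula without continuity correction, mean proportion 0.71:

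n = [1.96 × √(2 × 0.71 × 0.29) + 0.8416 × √(0.76 × 0.24 + 0.66 × 0.34)]² / 0.10²
= (1.2577 + 0.5368)² / 0.01 = 322.04 per arm.

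Design effect = 1 + (10 − 1) × 0.05 = 1.45. Then 322 × 1.45 = 466.9, so 467 per arm and 934 in total. This matches the plan.

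**Step 2: is there slack at full retention?** Effective size is 467 / 1.45 = 322.1 per arm, and power is 80.0%. There is none.

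**Step 3: has loss been built in through the class size?** The Background section reports 364 pilot participants in 36 classes, and 364 / 36 = 10.1. The value m = 10 therefore matches students who entered the pilot, not students followed up. No loss is hidden there.

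**Step 4: power with 934 enrolled and a fraction f lost.**

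Power = Φ{[0.10 × √n_eff − 1.96 × √(2 × 0.71 × 0.29)] / √(0.1824 + 0.2244)}

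Two patterns of loss bracket the result:
- Whole classes lost: n_eff = 467(1 − f) / 1.45.
- Loss spread within classes, which shrink to 10(1 − f): n_eff = 467(1 − f) / {1 + [10(1 − f) − 1] × 0.05}.

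| Assumed loss | Analysed per arm | Whole classes lost: n_eff, power | Loss within classes: design effect, n_eff, power |
|---|---|---|---|
| 0% | 467 | 322, 80.0% | 1.45, 322, 80.0% |
| 5% | 443.6 | 306, 78.0% | 1.425, 311, 78.7% |
| 10% | 420.3 | 290, 75.7% | 1.40, 300, 77.2% |
| 20% | 373.6 | 258, 70.7% | 1.35, 277, 73.8% |
| 30% | 326.9 | 225, 64.9% | 1.30, 251, 69.6% |

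Worked line for 20% loss within classes: n_eff = 373.6 / 1.35 = 276.7; (0.10 × 16.64 − 1.258) / 0.638 = 0.636; Φ(0.636) = 73.8%.

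**The case against.** **The size of the shortfall is unknown.** This stands. No retention figure is given, and at 5% loss the shortfall is only 1–2 points. The plan also has a feature that favours retention: a reward of 10 Swiss Francs tied to taking part at both baseline and follow-up. Assessing intact classes in lesson time may help too. A reader might infer that the trial is seriously underpowered, but the documents do not support that. They support only the statement that 80% needs complete follow-up.

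**The planned analysis is not the chi-square test.** This stands in part. The analysis uses GEE, possibly with baseline covariates, and drinking frequency is measured at baseline. Adjustment, or baseline predictors in the imputation model, could recover some of the lost information. Imputation keeps every student in the analysis but does not in general restore all that an unobserved outcome would have given. The sample size section rests on an unadjusted chi-square test and neither claims nor quantifies such a gain.

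**The intervention rate could be below 66%.** That is not a reserve against loss. The calculation is made at 66%, which is already more favourable than the pilot's fall from 76% to 68%.

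**Further inferences to avoid.** One is that the calculation is wrong; it is not. Another is to read the pilot's 76% participation (364 of 477 invited) as a retention rate; it describes uptake at invitation. A third is to add a penalty for unequal class sizes; the documents give no spread of class size on which to base one.

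**Conclusion.** The point holds as an omitted planning assumption, not as a calculation error. The number required for analysis is used as the number to enrol, although the plan itself anticipates missing 6-month outcomes. The stated 80% therefore applies only under full retention.

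How far power falls depends on a loss rate that the documents do not give and on whether loss takes whole classes or thins them. The figures also rest on the plan's 76% versus 66%, its intra-cluster correlation of 0.05 and the unadjusted test.

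A reader might go further and conclude that exactly 934 students must be analysed whatever happens, which fixes a larger enrolment target. That does not follow. If loss thins classes, the design effect falls and fewer analysed students suffice. At 20% loss, dividing 467 by 0.8 and rounding up gives 584 per arm, or 1,168 enrolled. Allowing for the smaller classes gives 322 × 1.35 = 434.7, so 435 analysed and 435 / 0.8 = 543.75, so 544 per arm, or 1,088 enrolled. The documents do not say which pattern to expect, so no single corrected target can be derived from them.

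**What to change.** In the Sample size calculation section, make three additions:

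1. Say that 934 assumes complete follow-up at 6 months.
2. State the retention expected at 6 months and its basis.
3. Restate the power for 934 enrolled at that retention. If 80% retention were expected, for example, the text would give about 71–74%, the lower end if whole classes drop out and the upper end if loss is spread within classes.

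If the sponsor expects baseline adjustment to offset part of the loss, that gain should be stated and justified in the same place.

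The cost is a few sentences and a less favourable stated power. No change to the assessment procedure or the design is needed.

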### Intervention

#### Technological background

The *MobileCoach Alcohol* was developed on the *MobileCoach* system. This is a modular system that allows an author to easily modify and optimize the single modules without any technical programming skills: e.g., the baseline assessment survey, the tailored web-based feedback, the intervention rules and content elements. The source code of the *MobileCoach* system will be made available as open source project on http://mobile-coach.eu by the end of 2014.

Building on the foundations of automata theory [26], the technical design of the *MobileCoach* system follows the concepts of a state machine that uses intervention rules for state transitions, which can be referred to as a fully automated expert system. Here, the state is an aggregate of all relevant attributes related to the intervention progress of a participant (e.g. the messages received or answers provided) whereas state transitions triggered by intervention rules lead to a change in these attributes and thus, to a state change. In particular, each participant of the intervention group is assigned to a particular intervention state based on her answers during the baseline assessment. In response to this assessment, a web-based feedback is generated individually by the system for each participant. Then, depending on a participant’s regular text message feedback during the subsequent 3 months, intervention rules trigger state transitions and the tailoring of the follow-up text messages. In particular, intervention rules are traversed once a day for each participant, and, as a result, update the state of the corresponding participant and fire text messages in the form of a question, a feedback text or a recommendation.

The technical architecture of this rule-based state machine is derived from the *model-view-controller* design pattern [27]. It consists therefore of (1) a persistence layer, i.e. the *model* based on the document database mongoDB (https://www.mongodb.org) and plain files for storing the intervention content including a detailed protocol of all incoming and outgoing text messages, (2) an application layer, i.e. the *view* based on the Vaadin web application framework (http://www.vaadin.com) with the template-engine Mustache (http://mustache.github.io) for intervention administration and the assessment survey at the baseline and, finally (3) a service layer, i.e. the primary controller that utilizes the Java programming language (http://java.com) and the expression evaluator Javaluator (http://javaluator.sourceforge.net) for the evaluation of the intervention rules. Password protection and Secure Sockets Layer (SSL) encoding will be used to ensure the privacy and safety of data transfer.

#### Theoretical background

The web-based part of the intervention provides normative feedback based on the social norms approach [12], which constitutes the theoretical background of the majority of evidence based internet interventions to reduce problem drinking in young people [15, 28].

The text messaging based part of the intervention also includes elements of the social norms approach (e.g., individual risk patterns of alcohol related negative consequences). However, it primarily relies on socio-cognitive constructs from major psychological models of health behaviour change, such as the Social Cognitive Theory [29] and the Health Action Process Approach [30]: outcome expectations, self-efficacy and planning processes. Within both models, positive outcome expectations, e.g., beliefs about the likelihood and value of the consequences of drinking less alcohol, substantially contribute to forming an intention to perform a desired action. Furthermore, self-efficacy, e.g., beliefs about the personal ability to resist alcohol in different drinking situations, is crucial in forming an intention to perform a desired action. Planning processes such as if-then plans that link situational cues with responses that are effective in attaining a desired outcome [31] are seen as particularly relevant to bridge the intention-behaviour gap and to translate behavioural intentions into actions.

#### Web-based feedback

The web-based feedback was already developed for a previous study [22]. Its interventional content is based on effective social norms intervention programs developed primarily for college and university students in the USA and Canada [32, 33] that had been modified for the target group of German-speaking adolescents in Switzerland aged 16 to 20 with different educational backgrounds. Age- and gender-specific norms for alcohol consumption were derived from a previous study [34] that assessed heavy drinking occasions, alcohol volume and the maximum number of drinks on a single occasion among 973 vocational and upper secondary school students in the Canton of Zurich, Switzerland. The web-based feedback includes individually tailored graphical and textual information concerning (1) the number of drinks consumed per week in relation to the age and gender-specific reference group (2) financial costs of drinking, (3) calories consumed with alcoholic drinks and (4) number of RSOD occasions in relation to the age and gender-specific reference group.

#### Text messages

On the first level, the content and number of the provided text messages will be tailored according to baseline drinking patterns. Participants will be assigned to one of three risk groups: (1) “Low-Risk”: no RSOD occasion during the last 30 days; (2) “Medium-Risk”: 1 or 2 RSOD occasions during the last 30 days and (3) “High Risk”: > 2 RSOD occasions during the last 30 days.

On the second level, the content of the text messages will be tailored according to the individual values on the following baseline variables: sex, motivation for reduced alcohol consumption, alcohol-related problems, typical drinking day and time, peak blood alcohol concentration during the previous 30 days, positive outcome expectancies, typical drinking situations, strategies to resist alcohol in different drinking situations, place of assessment (Canton Zurich vs. Canton Berne). Participants from all risk groups will receive text messages for a period of 3 months.

Participants of the low-risk group will receive one weekly text message providing information from the following content categories:Motivation for drinking within low-risk limits using individual data on positive outcome expectancies derived from [35].Strategies to resist alcohol in different drinking situations using individual data from the adolescent version of the Drinking Refusal Self-Efficacy Questionnaire (DRSEQ-RA) [36].

Participants of the medium-risk group will receive two weekly text messages. One weekly text message will be sent on a fixed weekday in the afternoon. It will provide information from one of the following content categories:Motivation for drinking within low-risk limits using individual data on positive outcome expectancies derived from a list provided by [35].Alcohol-related problems using individual data on previous alcohol-related problems.Peak blood alcohol concentration and related risks using data on sex, body weight and maximum number of drinks on a single occasion in the previous month.

Additionally, they will receive one weekly text message sent on the individually indicated typical drinking day and time. This text message focuses on the following aspects:4.Strategies to resist alcohol in different drinking situations using data on individual drinking situations and individual chosen strategies to resist alcohol. Participants will be asked at baseline to select 3 among 9 provided drinking situations, derived from [36], that are chosen as most tempting. For each of the 3 chosen drinking situations, they can choose 1 out of 3 strategies to resist alcohol. The resulting strategies are “if-then” plans based on the concept of implementation intentions [31], e.g., “When I am at a party, I will keep track of the amount I drink. I decide how much I will drink ahead of time and stick to this limit”.

Like participants of the medium-risk group, participants of the high-risk group will also receive two weekly text messages from the content categories (1) – (4). Additionally, they will receive information about local outpatient services for alcohol counselling using data on the place of assessment. Sample text messages for different risk groups and content categories are shown in Table 1.

**Table 1 Tab1:** **Sample text messages derived from individual data**

Risk group	Content category	Considered individual data	Resulting text message
Low-risk	Motivation for drinking within low-risk limits	Indicated “Yes” for the item: “If I drink within low-risk limits, other people will respect me”.	Hi Lisa. Great! You are not just a follower who drinks alcohol to fit in. That’s a smart decision. It shows strength of character and can even impress others.
Medium-risk	Strategies to resist alcohol in different drinking situations	Individually chosen if-then plan to resist alcohol in the tempting drinking situation “party”: “When I am at a party, I have soft drinks every now and then”.	Hey Luca. Congratulations! It’s a good decision to have soft drinks every now and then, when you are at a party! Non-alcoholic drinks provide your body with important minerals and are a thirst-quenching alternative.
High-risk	Local outpatient services for alcohol counselling	Place of assessment: Zurich	Hi Robin. Are you concerned about your own alcohol intake or that of a friend? Talking to someone about it can be really helpful. The website http://www.alcocheck.ch can offer you support. Write an e-mail to [contact] or call [name].

### Assessments and outcomes

At baseline, demographic variables (age, gender, educational level, and migration background) as well as characteristics of the schools and school classes will be assessed.

Baseline- and follow-up assessments will include:Frequency of RSOD occasions in the last 30 days (“How often did you have 5 (male; female: 4) or more drinks on one occasion in the last 30 days?”).Quantity of alcohol consumption, assessed by a 7-day drinking calendar similar to the Daily Drinking Questionnaire (DDQ) [37], for which participants were asked to think about a typical week in the past month and, for each day, to record the number of standard drinks they typically consumed on that day.Peak blood alcohol concentration assessed by asking participants to report the number of standard drinks consumed and the duration of their heaviest drinking episode in the previous 30 days. This information will be used along with the sex and weight to calculate an estimated peak blood alcohol concentration based on the Widmark Formula [38].Normative misperceptions of alcohol consumption using reference data from [39] and items derived from [14], who used modified versions of the first and second AUDIT-C [14, 40] items: “How often does a typical (male/female) secondary school student have a drink containing alcohol?” and “How many drinks does a typical (male/female) secondary school student have on a typical day when drinking alcohol?”.

The primary outcome of the planned study is RSOD in the past 30 days preceding the follow-up assessment. Secondary outcomes are (1) frequency of RSOD occasions in the past 30 days preceding the follow-up assessment, (2) peak blood alcohol concentration in the previous 30 days, (3) number of standard drinks consumed in a typical week of the preceding month, and (4) normative misperceptions of alcohol consumption in an age- and gender-specific reference group.

